## Abstract

**Background:**

Musculoskeletal disorders are one of the most important causes of work disability. Various rehabilitation services and return-to-work programs have been developed in order to reduce sickness absence and increase sustainable return-to-work. As the effects of conventional medical rehabilitation programs on sickness absence duration were shown to be slight, work-related medical rehabilitation programs have been developed and tested. While such studies proved the efficacy of work-related medical rehabilitation compared with conventional medical rehabilitation in well-conducted randomized controlled trials, its effectiveness under real-life conditions has yet to be proved.

**Methods/Design:**

The cohort study will be performed under real-life conditions with two parallel groups. Participants will receive either a conventional or a work-related medical rehabilitation program. Propensity score matching will be used to identify controls that are comparable to treated work-related medical rehabilitation patients. Over a period of three months, about 18,000 insured patients with permission to undergo a musculoskeletal rehabilitation program will be contacted. Of these, 15,000 will receive a conventional and 3,000 a work-related medical rehabilitation. We expect a participation rate of 40 % at baseline. Patients will be aged 18 to 65 years and have chronic musculoskeletal disorders, usually back pain. The control group will receive a conventional medical rehabilitation program without any explicit focus on work, work ability and return to work in diagnostics and therapy. The intervention group will receive a work-related medical rehabilitation program that in addition to common rehabilitation treatments contains 11 to 25 h of work-related treatment modules. Follow-up data will be assessed three and ten months after patients’ discharge from the rehabilitation center. Additionally, department characteristics will be assessed and administrative data records used. The primary outcomes are sick leave duration, stable return to work and subjective work ability. Secondary outcomes cover several dimensions of health, functioning and coping strategies.

**Discussion:**

This study will determine the relative effectiveness of a complex, newly implemented work-related rehabilitation strategy for patients with musculoskeletal disorders.

**Trial registration:**

German Clinical Trials Register (DRKS00009780, February 10, 2016).

## Background

About 35 million people aged 15 to 64 (11.0 %) in the European Union are limited in the work they can do because of a long-standing health problem or a basic activity difficulty [1]. As musculoskeletal disorders are still one of the most important causes of work disability, various rehabilitation services and return-to-work programs have been developed and implemented in order to battle the consequences of musculoskeletal disorders for the opportunity to participate in working life [2]. As shown by systematic reviews, such programs and interventions indeed may significantly reduce sickness absence and increase sustainable return-to-work, especially if they include work-related elements [3–5].

In Germany, rehabilitation programs for musculoskeletal disorders are usually provided as three-week in- or outpatient interventions under the umbrella of the German Pension Insurance (GPI). The treatment is multi-professional and follows evidence-based therapy recommendations [6]. However, change in sickness absence duration was shown to be slight in meta-analyses of observational studies [7, 8]. One randomized controlled trial indicated no effect on sickness absence duration [9]. Moreover, several studies revealed that patients with severe restrictions of work ability (e.g. long-term sick leave, poor return-to work expectation) have a considerable risk of not returning to work despite participating in a conventional medical rehabilitation (CMR) program [10, 11]. Therefore, work-related medical rehabilitation (WMR) programs have been developed and tested in recent years [10, 12].

These programs were designed to particularly support patients with severe restrictions in terms of ability to work. WMR programs regularly comprise a diagnostic assessment that compares job demands and patients’ work capacity and offer therapeutic interventions such as work hardening and work-related functional capacity training, work-related psychosocial groups and intensified social counseling [13–16]. A meta-analytic synthesis of randomized controlled trials that compared WMR and CMR programs in Germany provides robust evidence that in patients with musculoskeletal disorders WMR programs achieve higher rates of sustainable return-to-work and reduce sickness absence after one year. WMR participants had 2.4 times higher odds of sustainable return-to-work after one year and also reduced sickness absence [17].

To support nationwide implementation of such programs and to improve rehabilitation outcomes, the GPI developed a WMR guideline. This guideline defines inclusion criteria for WMR (e.g. long-term sick leave, poor self-rated return-to-work expectation, unemployment) and important diagnostic and therapeutic measures in WMR (see Treatment section for a more detailed description of WMR) [13, 18]. The implementation of the WMR guideline was evaluated in patients with musculoskeletal disorders in seven rehabilitation centers. The results showed that the implementation was challenging but feasible. Moreover, the observational study showed a significant reduction of sick leave for WMR participants, and more work-related interventions predicted shorter sickness absence at the three-month follow-up [19]. However, findings also indicated that allocation and treatment decisions (WMR vs. CMR) only partly followed the guideline recommendations [20].

While studies proved the efficacy of WMR compared with CMR in well-conducted randomized controlled trials with high treatment fidelity and carefully selected patients, the effectiveness of WMR under real-life conditions has yet to be proved. Interventions that work in efficacy studies may not necessarily also do well in real-world applications [21, 22]. Though reliable efficacy studies are a necessary condition for evidence-based practice, patients and other stakeholders may be most interested in the effectiveness of real-world services. While a randomized controlled trial is the gold standard and the most robust way to prevent allocation bias in efficacy studies, other designs and methods may be needed to evaluate the effectiveness of an intervention, especially, as in the case of WMR, where nationwide dissemination is completed and programs and allocation procedures are established. Nevertheless, as the WMR guideline clearly describes the patients in need and proposes several screenings to identify these patients [11], allocation bias is a severe challenge in determining an unbiased treatment effect estimate. One proper evaluation design in this case is the use of observational data and a subsequent propensity score matched analysis to control for confounding. We therefore designed a cohort study to analyze the relative effectiveness of WMR compared with CMR. As current allocation procedures regarding WMR seem to be far from perfect and WMR and CMR patients have a considerable overlap, a propensity matched comparison was chosen to address allocation bias. We hypothesize that WMR reduces sickness absence and improves sustainable return-to-work and work ability ten months after rehabilitation (primary outcomes) compared with CMR. Moreover, we expect to see evidence of the superior effectiveness of WMR regarding several secondary outcomes. The study protocol has been prepared according to the SPIRIT checklist (Standard Protocol Items: Recommendations for Interventional Trials) [23].

## Methods

### Study design

The study is a cohort study under real-life conditions with two parallel groups. Participants will either receive a WMR or a CMR program in one of the 256 approved rehabilitation departments. The allocation ratio is determined by the actual allocation under real-life conditions of rehabilitation service provision in Germany. The current ratio of WMR to CMR patients is approximately one to five. The investigators will not have any influence on allocation decisions. Current utilization of WMR is still considerably below the estimated number of patients who need it. Therefore, comparable controls are available who receive a CMR, though their severe restrictions in terms of work ability would also justify participation in a WMR program. Although the researchers have no influence on the allocation procedure they will have the opportunity to model treatment allocation by observed data. Thus propensity score matching will be used to identify controls that are comparable to treated WMR patients and to estimate the unbiased effects of the relative effectiveness of WMR compared with CMR. As randomized controlled trials confirmed the relative efficacy of WMR in trials with high treatment fidelity and carefully selected patients, and implementation of WMR is completed, we assume the superiority of WMR.

Baseline data will be assessed after approval of the rehabilitation program but before the patients begin their rehabilitation. Follow-up data will be assessed three and ten months after their discharge from the rehabilitation center. Moreover, administrative data records will be used. Additionally, department characteristics will be assessed by a departmental survey. No one will be blinded before, during or after the trial.

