### Participants

Patients are aged 18 to 65 years and have chronic musculoskeletal disorders, usually back pain. They have approval for rehabilitation either in an own rehabilitation institution of the Federal GPI or an institution that is leadingly occupied by the Federal GPI. Patients have requested rehabilitation because of health-related restrictions of work ability. Need for rehabilitation was acknowledged by a registered doctor and approved by the Federal GPI. Allocation to CMR and WMR is primarily decided by the socio-medical service of the Federal GPI. The socio-medical service may consider the findings of standardized screening which is usually part of the application documents and estimates the risk of not returning to work [11].

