### Statistical analysis

#### Propensity score matching

Patients of WMR and CMR will be matched by propensity scores to achieve balanced sample characteristics and to calculate unbiased estimates of relative effectiveness [22, 48–54]. The propensity score is the conditional probability of receiving the treatment under evaluation (i.e. WMR) given the vector of observed background variables. Matching by propensity scores enables balanced characteristics of the treated and the untreated sample if there is sufficient overlap of the propensity scores of both groups. Compared with a conventional direct matching procedure the problem of multidimensionality in finding a corresponding control, for instance related to age, sex, sickness absence duration, pain, depression and others, is thereby reduced to one dimension only.

The propensity score will be estimated by a logistic regression model including all variables that are associated with the treatment allocation. For every WMR participant a patient with a similar propensity score will be selected from the larger pool of CMR patients. Resampling will be realized without replacement. If necessary to achieve balanced data, a caliper of one-quarter of the propensity score during resampling will be used. For sensitivity analysis, additional matching schemes will be tested (with and without replacement, different calipers, varied number of controls). As an indicator of the bias before and after matching owed to differences related to the observed sample characteristics the standardized percentage bias will be calculated. This is the difference of the sample means in cases and controls relative to the square root of the average of the sample variances in both groups [55]. Multiple imputations will be used to fill in missing data before estimation of the propensity score. The propensity scores for each record will be averaged across the completed datasets, and propensity score matching will be performed with these averaged scores [56].

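### Matching on observed variables is said to give unbiased effects; that holds only if no unmeasured confounding remains, and the named checks cannot show how fragile the result is to that assumption

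*Protocol article*

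**What the plan says.** Study design gives the purpose of matching as finding comparable controls and "to estimate the unbiased effects of the relative effectiveness of WMR compared with CMR". The Propensity score matching section says that patients will be matched "to achieve balanced sample characteristics and to calculate unbiased estimates of relative effectiveness". 

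Both sections describe a score made from measured data. The researchers do not control allocation, but "they will have the opportunity to model treatment allocation by observed data"; the score is a probability "given the vector of observed background variables". The only condition attached is sufficient overlap of the scores, and it is attached to balance. The bias indicator (standardized percentage bias) is confined to observed characteristics. The stated robustness work is: "For sensitivity analysis, additional matching schemes will be tested (with and without replacement, different calipers, varied number of controls".

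On how patients reach a programme, the Participants section says: "Allocation to CMR and WMR is primarily decided by the socio-medical service of the Federal GPI". The service may take a standardized screening into account. The Background reports that, in an earlier evaluation, allocation followed the guideline only in part, and it concedes that "allocation bias is a severe challenge in determining an unbiased treatment effect estimate".

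**The concern.** Matching on a propensity score balances what went into the score. It yields an unbiased effect only under the further assumption that no unmeasured factor affects both the choice of programme and the outcome. The article never states that assumption next to its claim, so it asserts a property that the design cannot guarantee.

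The setting makes the assumption matter. Someone outside the study decides, with discretion, from an application file. Most covariates come instead from a patient questionnaire sent after approval. The plan relies on imperfect allocation to supply comparable controls, but does not ask why similar-looking patients were sent to different programmes.

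Changing replacement, caliper or number of controls leaves the covariate set as it is. If those analyses agree, that says nothing about what was not measured, and it may reassure wrongly. The target effect is small, so a net bias that is small on the outcome scale could alter the conclusion in either direction.

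**Working it through.** **Inputs** (Sample size estimation): 900 matched patients per group, cluster size 7.0, intracluster correlation 0.05, power 0.80, significance level 0.016, detectable SMD 0.175. Sidedness is not stated. The bias sizes below are assumptions, because the document gives none.

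**Step 1: reproduce the plan's figure.**
- Design effect = 1 + (7.0 − 1) × 0.05 = 1.30
- Effective n per group = 900 / 1.30 = 692.3
- SE = √(2 / 692.3) = 0.05375 SD
- Detectable SMD, two-sided = (2.409 + 0.842) × 0.05375 = 0.1747, which matches 0.175. A one-sided test gives 0.161 and does not match.
- Smallest significant observed SMD = 2.409 × 0.05375 = 0.129

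**Step 2: effect of a net residual bias b on the outcome scale.** With no true effect, P(significant) = P(Z > 2.409 − b/SE) + P(Z < −2.409 − b/SE). For bias against WMR, power at a true SMD of 0.175 is P(Z > 2.409 − (0.175 − b)/SE).

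| Net bias b (assumed) | False-positive rate, no true effect | Power at SMD 0.175 if the bias is against WMR |
|---|---|---|
| 0 | 1.6% | 80% |
| 0.05 SD | 7.0% | 47% |
| 0.10 SD | 29% | 16% |

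Example for b = 0.05: b/SE = 0.930 and 2.409 − 0.930 = 1.479, giving 6.96% in the upper tail plus 0.04% in the lower, together 7.0%. Power with the bias reversed: (0.175 − 0.05)/0.05375 = 2.326 and P(Z > 2.409 − 2.326) = 47%.

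The false-positive column describes a spurious WMR benefit only if the bias favours WMR. With the bias at 0.05 SD against WMR, the chance of a false result in favour of WMR falls from 0.8% to 0.04%.

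**Step 3: what kind of unmeasured factor produces such a bias.** Write b = γ × d, where γ is the change in outcome (in SD) per SD of the factor, beyond the matched covariates and baseline score, and d is its imbalance in SD left after matching. Both are assumed.

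| γ | d | b | False-positive rate |
|---|---|---|---|
| 0.1 | 0.2 | 0.02 | 2.4% |
| 0.3 | 0.1 | 0.03 | 3.4% |
| 0.3 | 0.2 | 0.06 | 9.8% |
| 0.3 | 0.3 | 0.09 | 23% |
| 0.5 | 0.2 | 0.10 | 29% |

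To create the whole planned SMD from bias alone, d = 0.175/γ: 0.58 SD at γ = 0.3, or 0.35 SD at γ = 0.5.

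**Step 4: the same fragility as an E-value.** Using RR ≈ exp(0.91 × SMD) and E = RR + √(RR × (RR − 1)):
- Observed SMD 0.175: RR = 1.173, E = 1.62
- Lower 98.4% limit, 0.175 − 0.129 = 0.0455: RR = 1.042, E = 1.25

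These conversions suit the two metric primary outcomes. Stable return to work is binary and needs its own scale.

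**The case against.** The strongest reply is that the covariates are unusually well chosen. Both screening scores used in Germany to judge need for WMR (SIMBO and the Würzburger Screening) are collected at baseline. The screening the service may consider is cited to the same source as SIMBO. The guideline criteria given as examples in the Background are also measured before rehabilitation starts: sick leave over the previous 12 months, employment status and return-to-work expectation. The outcome models adjust for the baseline score. All this stands and lowers the likely residual bias. It does not bring it to zero, because the service only *may* use the screening and the criteria did not fully explain allocation.

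The wording is also softened nearby: the text speaks of observed data and names allocation bias as a serious problem. That is true, but the condition is never joined to the claim in either place.

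Three stronger readings are tempting and are not supported.
- *Hidden selection would show up as a WMR benefit.* The direction is not fixed. WMR is aimed at patients at higher risk of not returning to work, so leftover confounding could equally work against it.
- *A small difference between patients is enough.* The 0.05 and 0.10 SD figures are net bias on the outcome. A weak factor with modest imbalance takes the error rate only from 1.6% to 2.4%.
- *The trial has no hidden-bias analysis at all.* A condensed article may leave that to an analysis plan that is not shown. What can be said is that the sensitivity set stated here cannot address the question.

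**Conclusion.** The point stands as an overclaim coupled with a stated sensitivity set that cannot test it. The estimate is adjusted for measured covariates and is unbiased only if no unmeasured confounding remains; two sections say otherwise without condition. The exposure is moderate. A net bias of one to two standard errors (0.05 to 0.10 SD) is enough to change the error rates materially, but reaching it takes a moderately strong factor that stays imbalanced after matching.

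The figures rest on the plan's own sample size and clustering assumptions, a two-sided test, a metric outcome, and bias sizes that are assumed. They show sensitivity; they do not show that bias of this size is present. Nor does the article contain a rule for how the result will be reported, so a reader should not infer that a biased estimate is certain to be presented as proof.

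**What to change.** 1. In Study design and in Propensity score matching, replace the word unbiased with: adjusted for measured covariates, and unbiased only if no unmeasured confounding remains.
2. Add to the sensitivity analyses in Propensity score matching one hidden-bias analysis for each of the three primary outcomes. Rosenbaum bounds would serve, or E-values for the estimate and the confidence limit, on a scale suited to each outcome, including the binary one. These methods do not detect hidden bias; they state how much would be needed to change the conclusion.
3. Report it beside the primary result whether that result is positive or null. For a null result, the relevant question is how much bias against WMR would have masked the planned SMD of 0.175.

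Cost: a change of wording in two places and a short extra analysis on data already planned. The downside is a more cautious conclusion.

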### Study setting

All included rehabilitation centers are located in Germany. Rehabilitation services may be provided as inpatient or outpatient programs. Most of the departments are inpatient centers. There are some outpatient departments that are mainly located in major cities. Participation in a rehabilitation program was approved by the Federal GPI. In both groups, interventions will be performed by rehabilitation physicians, psychologists, physiotherapists, sports therapists, social workers, occupational therapists and other health professionals.

The duration of the rehabilitation program is initially determined by the Federal GPI (usually about three weeks). The rehabilitation center and the patient may arrange to extend the program. By request the patient may stop the rehabilitation program ahead of schedule.

### Treatment

#### Control

Participants of the control group will receive a CMR program according to current treatment standards and guidelines for the rehabilitation of musculoskeletal disorders. CMR programs last approximately three weeks. The daily quantum of therapy amounts to three or four hours. Following a multimodal approach, CMR programs include sports and exercise therapy, physiotherapy, occupational therapy, massage and other physical therapies, social and psychological counseling, patient education, pain management and relaxation training. CMR programs focus on the functional limitations of the musculoskeletal system and aim to restore physical abilities to promote participation in work and daily living. However, in contrast to WMR programs, they do not integrate an explicit focus on work, work ability and return to work in diagnostics and therapy.

#### Intervention

Participants of the intervention group will receive a WMR program according to the guideline for WMR [13, 18] as well as to the current treatment standards and guidelines for the rehabilitation of musculoskeletal disorders. WMR programs last approximately 2.4 days longer than CMR programs since they contain 11 to 25 h of work-related treatment modules [17]. Like CMR programs WMR programs follow a multimodal approach that comprises sports and exercise therapy, physiotherapy, occupational therapy, massage and other physical therapies, social and psychological counseling, patient education, pain management and relaxation training. However, WMR programs more explicitly focus on work, work ability and return to work. Thus, they include intensified work-related diagnostics as well as work-related functional capacity training, work-related psychosocial groups and intensified social counseling. Intensified work-related diagnostics identify individual needs by comparing work-related physical and psychosocial functional capacity with the patient’s job demands. Assessment of functional capacity is performed by means of a short functional capacity evaluation and questionnaires. Demands will be assessed by job analysis. Matching of capacity and demands is supported by standardized assessments [24–26]. Work-related functional capacity training exercises specific movements and postures according to individual workplace conditions. Work-related psychosocial groups deal with the mutual dependence of behavioral and emotional health experiences and the workplace environment. Additionally, preventative measures like stress management or conflict management in dealing with psychosocial stressors are taught. Finally, intensified social counseling examines the individual work-life situation and provides socio-legal guidance and advice concerning further assistance within the social security system.

